# Comparative effectiveness of adding weight control simultaneously or sequentially to smoking cessation quitlines: study protocol of a randomized controlled trial

**DOI:** 10.1186/s12889-016-3231-6

**Published:** 2016-07-22

**Keywords:** Smoking, Weight management, Combined treatment, Simultaneous, Sequential, Quitlines

## Abstract

**Background:**

Prevalence of multiple health risk behaviors is growing, and obesity and smoking are costly. Weight gain associated with quitting smoking is common and can interfere with quit success. Efficacy of adding weight management to tobacco cessation treatment has been tested with women in group sessions over an extended period of time, but has never been tested in real-world settings with men and women seeking help to quit. This paper describes the Best Quit study which tests the effectiveness of delivering tobacco and weight control interventions via existing quitline infrastructures.

**Methods:**

Eligible and consenting smokers (*n* = 2550) who call a telephone quitline will be randomized to one of three groups; the standard quitline or standard quitline plus a weight management program added either simultaneously or sequentially to the tobacco program. The study aims to test: 1) the effectiveness of the combined intervention on smoking cessation and weight, 2) the cost-effectiveness of the combined intervention on cessation and weight and 3) theoretically pre-specified mediators of treatment effects on cessation: reduced weight concerns, increased outcome expectancies about quitting and improved self-efficacy about quitting without weight gain.

Baseline, 6 month and 12 month data will be analyzed using multivariate statistical analyses and groups will be compared on treatment adherence, quit rates and change in weight among abstinent participants. To determine if the association between group assignment and primary outcomes (30-day abstinence and change in weight at 6 months) is moderated by pre-determined baseline and process measures, interaction terms will be included in the regression models and their significance assessed.

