### Measures

Data for analyses will come from information collected when a person registers with the quitline, baseline data collected by a quit coach, 6 and 12 month phone or on-line follow-up data collected by a survey team and Alere’s tracking information on number and duration of counseling calls completed.

**Primary outcome measures** will be self-reported 30-day point prevalent abstinence and self-reported change in weight at 6 months.

**Secondary outcome measures** include 7-day point prevalence and continuous abstinence at 6 and 12 months, and reduction in amount smoked in continuing smokers. Other data will include descriptive and process data for analyses of mediators and moderators of intervention effects and cost data.

Survey content will be derived from standardized validated measures used to assess tobacco history, weight variables and outcomes, and from prior research findings and theoretical underpinnings of efficacious clinical trials [27, 33, 34, 37, 40, 50]. Most of the following measures will be assessed at baseline and/or 6 & 12 months and used to describe participants and evaluate outcomes.

*Demographics:* age, gender, race, ethnicity, education, height, weight, and other general demographics.

*Chronic Disease:* assessed by asking participants if they have ever been diagnosed with diabetes, heart disease, asthma, or a lung disease.

*Depressive symptoms:* measured with the PHQ-2, a 2 item screening measure for depressive symptoms that has demonstrated strong criterion and construct validity. The scale uses a 4-point response option to assess frequency of dysphoria and anhedonia. Sensitivity of the PHQ-2 has been reported at 84 %, with 72 % specificity for a cut score of 3 [51].

*Perceived stress:* measured with the 4-item Perceived Stress Scale (PSS), to assess the degree to which respondents find their lives to be stressful. The PSS has been shown to be a valid and reliable measure with alpha reliability coefficients from .84 to .86 [52]. PSS scores have been shown to be related to smoking relapse [53].

*Smoking/quit attempt history:* lifetime and current smoking, cigarettes smoked per day, history of quit attempts, prior use of nicotine replacement and other cessation treatments, and exposure to other household users.

*Nicotine dependence:* Fagerström Test of Nicotine Dependence (FTND) [54], which is the most commonly used measure for assessing nicotine dependence and is predictive of abstinence [55].

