To test whether changes attributable to the weight management program mediate the cessation rate, we will examine changes in weight concerns, weight, outcome expectancies on quitting, and self-efficacy in quitting without weight gain. Mediation implies a causal hypothesis whereby an independent variable (ie, the weight management program) causes a mediator (eg, reduced weight concerns) that causes a change in a dependent variable (ie, cessation) [64]. We will follow four steps to test mediation effects [65, 66]. For example, to assess whether reduced weight concerns mediates cessation, we must: (1) demonstrate significantly different cessation outcomes for weight management and comparison groups, (2) demonstrate differences in weight concerns by condition, (3) establish that reduced weight concerns is significantly related to cessation rate, and (4) show that the effect of a weight management intervention on cessation rate is significantly less after controlling for change in weight concerns. We will further test whether changes in outcomes expectancies of treatment on quitting, self-efficacy in quitting without weight gain, physical activity and diet (eg fruits and vegetables) mediate the effect of the weight management program on weight gain. Regression analyses will be conducted to examine the moderating effects on cessation and weight gain of baseline characteristics of BMI, age, gender, weight concerns, nicotine dependence, outcome expectancies and self-efficacy in quitting. Moderators will be included in the regression analyses as mean-centered covariates and as interaction terms with the combined treatment group indicator.

Exploratory analyses will also assess mediators of weight gain and whether baseline BMI, weight concerns, self-efficacy, outcome expectancies, nicotine dependence, use of medications, age and gender moderate the effectiveness of the different interventions for cessation and weight outcomes.

All analyses will be conducted using SAS or STATA software.

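### Process measures recorded after randomisation are planned as moderators, in conflict with the baseline-only list under Aim 3, and smoking reduction is compared only in continuing smokers; both are open to selection bias.

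*Protocol article*

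**What the plan says.** **Moderators.** The protocol article describes them in three places, and the lists differ.

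- Abstract, Methods: to learn whether the association of group with 30-day abstinence and weight change at 6 months "is moderated by pre-determined baseline and process measures, interaction terms will be included in the regression models and their significance assessed".
- Measures: "Other data will include descriptive and process data for analyses of mediators and moderators of intervention effects and cost data". The same section gives as a data source the operator's "tracking information on number and duration of counseling calls completed", and its treatment-utilisation item adds website and pharmacotherapy use.
- Statistical analysis plan, Aim 3: the main regressions examine "moderating effects on cessation and weight gain of baseline characteristics of BMI, age, gender, weight concerns, nicotine dependence, outcome expectancies and self-efficacy in quitting". All of these are baseline variables. A later exploratory paragraph asks whether "baseline BMI, weight concerns, self-efficacy, outcome expectancies, nicotine dependence, use of medications, age and gender moderate the effectiveness of the different interventions". No time point is attached to medication use.

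**Smoking reduction.** Measures lists among the secondary outcomes "reduction in amount smoked in continuing smokers". It is defined there as the change in cigarettes per day from baseline to follow-up, asked of those smoking at 6 or 12 months.

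The article describes no method for handling a moderator measured after randomisation, or for the continuing-smoker subset.

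**The concern.** Randomisation makes the arms comparable within levels of a variable that was fixed before allocation. It gives no such assurance within levels of a variable that allocation can change. Calls completed, website use and in-programme medication use are of that second kind. If an arm changes who completes calls, then completers in one arm differ in prognosis from completers in another, and an arm-by-process interaction mixes effect modification with self-selection and mediation. Fixing the list of process measures in advance does not make them pre-randomisation.

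Continuing smokers raise the same issue. Membership of that group is decided by smoking status at follow-up, which is close to the co-primary outcome. If combined treatment helps more people quit, the remaining smokers in those arms are a more selected group, so the comparison loses its randomised basis just when the treatment works.

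At stake are the secondary and explanatory conclusions: statements about which users benefit, and about whether the programme reduces consumption in those who do not quit.

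**Working it through.** **1. Are the process measures post-randomisation?** Study design says participants are randomised immediately after consent and baseline data, and then begin the intervention. Calls completed are therefore recorded after allocation. For medication use two readings exist: Measures collects earlier use of nicotine replacement and other cessation treatments as history, and also pharmacotherapy use through automated records. The second is likely for a moderator called use of medications, but the text does not settle it.

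**2. Could arm affect them?** Call content differs by arm (Table 1: integrated weight calls, later weight calls, or neutral topics), and the Abstract plans to compare groups on adherence. So dependence is possible, but not shown.

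**3. What would follow for a moderator test?** Illustration with all parameters assumed and 1,000,000 simulated people per scenario:

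- U is a standard normal prognostic trait and A is the arm (0 or 1).
- Process measure M = 1 if s·A + (0.8 + i·A)·U + logistic noise > 0.
- logit P(quit) = −1.1 + 0.8·U, so neither arm nor M has any effect.

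| Scenario | log OR for arm, M = 0 | log OR for arm, M = 1 |
|---|---|---|
| Arm does not affect M (s = 0, i = 0) | 0.006 | −0.010 |
| Arm shifts level of M (s = 0.5, i = 0) | −0.044 | −0.054 |
| Arm shifts level more (s = 1, i = 0) | −0.127 | −0.106 |
| Arm changes who takes up M (s = 0, i = −0.6) | 0.196 | −0.170 |
| Both (s = 0.5, i = −0.6) | 0.168 | −0.192 |

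The true value is 0 throughout. A level shift biases both strata by about the same amount and creates little false interaction. A change in who takes up M gives −0.170 − 0.196 = −0.366, an interaction odds ratio of exp(−0.366) ≈ 0.69 where the truth is 1.

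**4. What would follow for smoking reduction?** The quit rates come from Sample size and power analysis: control 29.6 % (the commercial rate) and the pooled combined arms 5.7 points higher, 35.3 %. The odds ratio is (0.353/0.647)/(0.296/0.704) = 1.298, which matches the stated 1.30. For 850 versus 1700 at two-sided 5 % (a level the article does not state), simulated Fisher's exact power is 80.9 %, so the stated 80 % reproduces.

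Assumed: latent dependence U is standard normal; the lowest p of U quit; reduction if still smoking has SD 8 cigarettes per day and correlation −ρ with U; arm has no effect on reduction.

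- Mean U in continuing smokers = φ(q)/(1 − p), with q = Φ⁻¹(p).
- Control: q = −0.536, 0.3456/0.704 = 0.491.
- Combined: q = −0.377, 0.3715/0.647 = 0.574.
- Spurious difference in mean reduction = −8 × ρ × (0.5743 − 0.4909) = −0.667ρ.

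| ρ | Combined minus control, cigarettes per day |
|---|---|
| 0 | 0 |
| 0.3 | −0.20 |
| 0.5 | −0.33 |
| 0.7 | −0.47 |

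The sign goes against the arm that helps more people quit.

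**5. How does that compare with sampling error?** With full follow-up, continuing smokers number 850 × 0.704 ≈ 598 in control and 1700 × 0.647 ≈ 1100 in the pooled combined arms. SE = √(64/598 + 64/1100) ≈ 0.41. For one combined arm (850 × 0.647 ≈ 550), taking the same quit rate, SE = √(64/598 + 64/550) ≈ 0.47. The illustrated bias is thus about 0 to 1.15 standard errors in the pooled comparison, and 0 to about 1 for a single arm.

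**The case against.** The strongest reply is that the operative plan is already mostly sound. The Aim 3 moderator regressions name baseline characteristics only. Process measures appear as moderators only in a phrase of the Abstract and in a general sentence on data use that covers mediators as well, and no particular process measure is named. Medication use is exploratory. The design also limits differences between arms: all have 10 calls, equalised to reduce unequal burden and dropout, and medication access follows the coverage plan or contract. Smoking reduction is one secondary outcome, openly defined as being among continuing smokers.

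Much of this stands. It lowers the stakes and rules out saying that bias is certain. It does not remove the point: the Abstract ties process measures to interaction tests on the primary outcomes, Measures repeats the moderator use, and both conflict with the Aim 3 list. Equal numbers of calls offered do not ensure equal or equally selected completion. An open definition of the continuing-smoker subset does not make it a randomised comparison.

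A reader might infer more: that every one of these variables is post-randomisation and that the comparisons are biased. The document does not support that. The timing of medication use is not given, and prior use is also collected. Bias vanishes if arm affects neither uptake nor quitting, or if these are unrelated to prognosis.

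**Conclusion.** The point holds as a risk and an inconsistency. Moderation by process measures is planned in two places and contradicted by the baseline-only list in the main moderator regressions. Medication use shares the problem only if in-programme use is meant. The continuing-smoker comparison of reduction is not protected by randomisation.

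The document does not allow the size to be derived. The range of 0 to about 0.5 cigarettes per day rests on an assumed SD of 8, assumed correlations of 0 to 0.7, quitting decided wholly by the latent trait, and the planned 5.7-point quit difference actually occurring. The false interaction in the moderator illustration likewise depends on arm changing who takes up the process measure.

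The primary arm comparison of abstinence is untouched. The change is worth making because it is cheap and because the article looks ahead to dissemination across quitlines, not because a large error has been shown.

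**What to change.** 1. Align the Abstract and Measures with Aim 3: restrict moderators to variables fixed at or before randomisation.
2. State when medication use is measured. In place of in-programme use, take prior medication use or eligibility at enrolment. The Statistical analysis plan already has an indicator of NRT qualification, but only for State quitline plans; extend it to commercial contracts where eligibility is recorded.
3. Report process measures descriptively by arm or as mediators, labelled non-causal.
4. Label smoking reduction in continuing smokers as descriptive. If an arm comparison is wanted, compare cigarettes per day at follow-up in all randomised participants, with abstainers set to 0 and adjustment for baseline cigarettes per day.

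**Cost.** Mostly wording. Baseline and follow-up cigarettes per day and prior medication use are already collected. The article does not show an eligibility variable for commercial participants, so that part may need a record check. The all-participant measure partly overlaps with abstinence and answers a somewhat different question from reduction among smokers.

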**Discussion:**

This study will generate information to inform whether adding weight management to a tobacco cessation intervention delivered by phone, mail and web for smokers seeking help to quit will help or harm quit rates and whether a simultaneous or sequential approach is better at increasing abstinence and reducing weight gain post quit. If proven effective, the combined intervention could be disseminated across the U.S. through quitlines and could encourage additional smokers who have not sought cessation treatment for fear of gaining weight to make quit attempts.

**Trial registration:**

Clinicaltrials.gov NCT01867983. Registered: May 30, 2013

**Electronic supplementary material:**

The online version of this article (doi:10.1186/s12889-016-3231-6) contains supplementary material, which is available to authorized users.

## Background

### Comorbid smoking and obesity are a public health problem

Obesity and smoking account for over three quarters of a million deaths per year in the U.S. [1–3] and about 92 % of smokers have at least one additional health risk behavior [4–8]. More than nine million adults are both obese and smoke [9], markedly increasing their mortality risk [2, 3]. Although effective smoking cessation treatments are available [10–13], weight gain following cessation is common [14–18]. Modest weight gain of about 8-10 lb is the norm, but some smokers gain more than 20 lb after quitting. There is evidence that obese smokers and smokers concerned about post-cessation weight gain may experience greater than average weight gain after quitting and cessation related weight gain can increase the risk for weight related health conditions [16, 19–24]. A systematic review of interventions focused on preventing post cessation weight gain confirmed prior research findings that 80–90 % of smokers gain weight after quitting; that only 10–20 % gain more than 10 kg and that the weight gain is generally permanent unless changes in lifestyle are adopted [25]. The authors concluded that there are very few interventions that entirely prevent post cessation weight gain, but there is evidence of modest effects for reducing the amount of weight gained.

### Efficacy of combined weight and cessation interventions has been established and can help smokers quit while minimizing weight gain

A systematic review of randomized controlled trials that compared combined behavioral smoking and weight management treatment with smoking treatment alone found that the combined interventions produced a significant improvement in cessation and reduced weight gain over tobacco treatment alone in the short term with a similar but non-significant trend at 6 or 12 months [26]. In this review by Spring and colleagues, 779 articles were identified from searching PubMed, Ovid MEDLINE, CINAHL, EMBASE, PsycINFO and Cochrane Central Register of Controlled Trials, and 10 trials met eligibility criteria and were included in the meta-analysis. Of the 2233 adults who participated (2079 females and 154 males), those who received both smoking and weight treatment showed increased abstinence [odds ratio (OR) = 1.29, 95 % confidence interval (CI) = 1.01, 1.64] and reduced weight gain (g = -0.30, 95 % CI = -0.57, -0.02) in the short term (<3 months) compared with patients who received smoking treatment alone. Differences in abstinence (OR = 1.23, 95 % CI = 0.85, 1.79) and weight control (g = -0.17, 95 % CI = -0.42, 0.07) were in the same direction but no longer significant in the long term (>6 months) [26]. One of these studies, also conducted by [name] and colleagues, showed that a sequential treatment approach which provided cessation treatment first, followed by weight management treatment, reduced weight gain to a greater extent than simultaneous treatment and cessation treatment alone and showed a non-significant trend for better cessation rates [27]. Similarly, Copeland and colleagues tested a sequential approach to weight management following two weeks of cessation treatment and found that individually tailored weight management resulted in higher cessation rates than group treatment. Groups did not differ in weight gain and the study did not have a tobacco cessation only treatment group [28]. According to the most recent Cochrane review, some smoking cessation interventions that included personalized weight management support or very low calorie diets may limit post cessation weight gain without harming abstinence rates, but only in the short term [29]. The review also reported that exercise interventions can reduce weight gain without undermining quit attempts over the long term and that bupropion and fluoxetine were better at suppressing weight gain than NRT but only while using the medications [29].

Most of the successful smoking cessation interventions designed to prevent cessation-related weight gain focused on calorie restriction or meal replacement, behavioral counseling on weight control, some form of exercise and/or cessation medications [29–35]. In addition to dietary and physical activity interventions, a weight acceptance approach has been tested in three trials [32, 36, 37]. The rationale behind this line of research stems from research findings that excessive concerns about weight gain can interfere with successful quitting. Thus the intervention aims to address maladaptive beliefs about weight, encourage acceptance of moderate weight gain and to focus on tobacco cessation. In the original weight concerns trial, Perkins found that adding an intervention aimed at addressing and reducing maladaptive weight concerns simultaneously with smoking cessation treatment resulted in a significant improvement in cessation, as compared to cessation treatment alone. Weight gain among those who quit smoking also differed across groups. At 6 and 12 months, weight gain was significantly lower for the weight concerns group [2.9 ± 2.6 kg and 2.5 ± 4.2 kg] compared with the weight control group [4.1 ± 4.8 kg and 5.4 ± 3.3 kg] and cessation only treatment [6.4 ± 3.5 kg and 7.7 ± 4.7 kg] [36]. The second weight concerns study involved a 2x2 randomized trial offering standard cessation alone vs. the weight concerns intervention crossed with placebo or bupropion. Results showed that among women offered bupropion to help with cessation, those randomized to the weight concerns intervention had significantly greater levels of abstinence at 6 months than did standard smoking cessation counseling combined with bupropion or placebo and a non-significant increase in weight gain at 6 months with no effect on weight at 12 months. A third trial of the weight concerns intervention tested the effectiveness of this weight acceptance approach in a population-based setting of a national tobacco quitline among 2000 male and female smokers seeking help to quit smoking. Results were published after the three systematic reviews and showed that at 6 months the intervention had a significant weight suppressive effect without impacting cessation [37].

These results highlight the difference between “weight concerns” interventions which strive to increase smoking cessation and are not consistently associated with weight suppression after quitting, and “weight loss/weight management” interventions involving diet or targeted behavioral weight loss approaches which do reduce weight gain. Overall, the aggregated findings in these reviews provide no evidence that combining smoking treatment and behavioral weight control undermines either abstinence or weight control and some evidence of benefit for both. Although systematic reviews have established that combining weight management with tobacco cessation treatments are a safe and moderately successful approach for reducing weight gain and improving cessation outcomes in the short term, most trials used intensive, in-person, group interventions and very few included males [25, 26, 29, 38]. Such intensive interventions are unlikely to be adopted at a population level, and if they were, would be unproven for half of the population. A sound knowledge base is needed to inform treatment decisions about best practices for the growing population with multiple health risk behaviors. Since the prior efficacy study conducted by Spring and colleagues suggests that sequential weight control treatment can suppress cessation related weight gain [27], there is a need to determine whether the prior finding is replicable in a population based setting and for both short and long-term tobacco and weight outcomes.

Quitlines provide an ideal setting in which to integrate tobacco cessation with recommended behavioral treatments for other health risk behaviors. Quitlines are freely available in all 50 states and the U.S. territories, have the potential to reach large populations of smokers and have proven to be effective and cost-effective [10–13, 39]. Quitlines offer a range of services including multiple counseling calls with cessation specialists, mailed support materials and access to modest regimens of nicotine patch or nicotine gum (NRT) [13, 39, 40]. Given the risk of both continued smoking and weight gain, it is worthwhile to test successful but intensive combined interventions adapted for population delivery via a telephone quitline. This paper describes the design, methods, adapted interventions and analytic approach for such a clinical trial. The rationale for our study is to replicate and scale the prior efficacy trial described by Spring that tested the simultaneous or sequential addition of weight control treatment compared with tobacco cessation treatment alone [27]. If a combined phone and web based weight control program added to a standard phone/web based cessation treatment had benefits for cessation and weight control, such a program would have substantial reach and public health benefit.

